### Type I complex regional pain syndrome and DRF

Resting pain and pain with activity are common aftereffect following DRF and have been documented to persist in 32.6 and 41.9% of cases respectively at two years post injury [20]. At the time of initial follow up after first definitive medical/surgical treatment of DRF, 81% of persons have been reported to describe having “severe” to “very severe” pain [15].

Type I complex regional pain syndrome (CRPS) is a condition that presents following an injury or illness where nerves are not damaged and is characterized by regional pain, increased sensitivity to touch, swelling, and impairment of motor function that are out out of proportion relative to the extent and location of the original injury/illness [21–24], and has been reported to occur in as many as 37% of persons who sustain DRF [25]. Jellad et al. [25] report that women are 5.8 times more likely than men to develop CRPS after DRF. Persons who sustain low to medium energy impact DRF are 7.7× more likely to develop CRPS than those who sustain high impact fractures, [25]. Additionally, Moseley et al. [26] report that persons with a 0–10 numerical pain scale (NPS) rating of greater than 4 within one week after closed reduction and casting for DRF were 15.1 times more likely to develop CRPS, than those with less than a 5/10 NPS rating.

Many theories exist on the mechanisms for developing Type I CRPS [27]. Recent evidence indicates that CRPS likely has a component mediated by the cerebral cortex [28, 29]. Neuroimaging studies have revealed CRPS-associated shrinkage of the areas of the primary somatosensory cortex (S1 and S2) that represent the painful limb [30, 31]. These cortical changes may be linked with pain sensitization [28, 30]. Other researchers have illustrated disinhibition of the motor cortex and a disrupted body schema in persons with CRPS [32, 33]. Peripheral sensorimotor changes such as those observed by Karagiannopoulos et al. [17] may be indicative of cortical changes occurring following DRF and cast immobilization.

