### Participants

To ensure that criteria for participation are met, patients will be recruited from outpatient clinics staffed by physicians specializing in Orthopaedic, Sports and Family Medicine. The clinics are associated with a large public university in the Midwestern United States. At the time of the first orthopaedic treatment for closed DRF, patients will be offered the opportunity to participate. Prior to enrollment and allocation, oral and written informed consent will be sought. We will seek to enroll 66 participants who have received closed treatment of a distal radius fracture. Through use of a block randomization method, participants will be allocated to a SOC intervention (*n* = 33) group or a SOC + mGMI (*n* = 33) group. Following the consent process, the PI, not a blinded evaluator or interventionist, will actuate the randomization through use of a random block assignment generator [49]. To ensure partcipants are and remain blinded to allotment, participants will be informed that they will be randomized to one of two “occupational therapy treatment approaches” and will be asked not to discuss their treatments with others enrolled in the trial. Evaluators will be blinded to allocation. The feasibility of enrolling these numbers is high given that from 2013 to 2015, the aforementioned Orthopaedics clinic alone cared for an average of 218 women a year who met the below described inclusion criteria. These numbers are likely attributable to the characteristics of the area served by this health system (i.e., urban, northern latitude with slippery weather conditions) which are associated with increased incidence of DRF [7, 9, 10]. The proposed flow of participants from enrollment to completion is reflected in Fig. 1.

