#### Inclusion criteria

The intent of this study is to target persons with high risk for developing CRPS. Therefore, it is limited to women with fragility or low-impact type fractures who are:55 years or oldermanaged with closed orthopaedic treatment and cast immobilizationreporting a numerical pain rating of greater than 3/10 within 1 week of initial medical management of their fracture

These patient factors are known to have strong associations with type I CRPS development [4, 26, 34].

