### Statistical analysis

Regarding the continuous primary outcomes (i.e., SF-MPQ, PRWHE) a sample size of 30 per group will give 81% power to identify as significant a mean difference of .75 SD in change in these outcomes between the two groups [72, 73]. A sample size of 30 per group will give 81% power to identify as significant a mean difference of 0.75 SD in change in continuous outcomes between the two groups. A sample size of per group will give 81% power to identify 20% vs. 58% as statistically significant for the Dichotomous outcome, Budapest diagnostic criteria. To adjust to an anticipated dropout rate of 10%, we will overenroll in each group by 3 bringing each group’s enrollment to 33. Following this adjustment, the total sample size will be 66 patients.

Data on recruitment, retention, therapy attendance, medication use, continuance of therapy beyond cast removal, and home program adherence will be expressed in terms of rates (e.g., rate of eligibility and randomization for those screened, rates of retention up to and including the final evaluation, and rates of satisfactory adherence to the intervention protocol). Simple descriptive statistics will be employed. Baseline demographics and characteristics will be summarized and compared between groups using Fisher’s exact test for categorical variables and, depending on whether or not parametric assumptions are met, either a two-sample *t*-test or Mann-Whitney U test for continuous variables.

Continuous variable outcomes (Primary: PRWHE, SF-MPQ; Secondary: Goniometry, grip dynamometry and JPS) will be analyzed using a mixed effects linear models to evaluate change over time between groups. Models will include a random effect to account for the within-subject correlation for repeated measurements, and fixed effects of group, time, and group by time interaction. Model assumptions will be examined before fitting models. If assumptions are not met, nonparametric test (Wilcoxon test) will be used. For dichotomous outcomes (diagnosis of CRPS), Fisher’s exact test will be performed to compare proportions between groups.

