In a manner consistent with that described of Walenkamp et al. [73], an achor-based approach to determining the MCID of the PRWHE and SF-MPQ will be taken through use of the Patient’s Global Impression of Change (PGIC) [74] scale as the anchor. The PGIC is a seven-point Likert scale, ranging from ‘very much improved’ to ‘very much worse’, and will be administered at the time of cast removal. The Minimal detectable change (MDC) of these two measures will be determined through use of the statistical methods described by Walencamp et al. [73].

All statistical analyses will be conductedby a PhD biostatistician who will employ the use of the Statistical Analysis System software (SAS, version 9.3, 2011; SAS Institute, Cary, NC). All analyses will be performed on an intent-to-treat basis. Two-sided tests with *p*-value less than 0.05 will be considered statistically significant.

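### The unadjusted Fisher's exact test fixed for the primary CRPS outcome is valid and correctly powered, but avoidably inefficient: it runs well under 5% and cannot use first-week pain

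*Protocol article*

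**What the plan says.** The Statistical analysis section fixes the CRPS test: "Fisher’s exact test will be performed to compare proportions between groups". No covariate or stratification is named for it. The level is set in the same section: "Two-sided tests with *p*-value less than 0.05 will be considered statistically significant". The power sentence says the sample "will give 81% power to identify 20% vs. 58% as statistically significant for the Dichotomous outcome, Budapest diagnostic criteria"; the number per group has dropped out of that sentence, but the neighbouring sentence for the continuous outcomes gives 30. Enrolment is 33 per arm: "To adjust to an anticipated dropout rate of 10%, we will overenroll in each group by 3 bringing each group’s enrollment to 33".

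On pain, the Background section on type I CRPS reports that people rated above 4/10 within a week of casting "were 15.1 times more likely to develop CRPS, than those with less than a 5/10 NPS rating". The Inclusion criteria require "a numerical pain rating of greater than 3/10 within 1 week of initial medical management of their fracture", so on a whole-number scale ratings from 4 to 10 are eligible. The Participants section describes block randomization and mentions no stratification by pain.

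**The concern.** Two features of the planned test cost power at a fixed sample size.

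- Fisher's test conditions on both margins. With about 30 per arm its attainable p-values are coarse, so its true type I error lies well below the declared 5%.
- It compares two raw proportions. It cannot use a baseline prognostic variable or correct a chance imbalance in one. The cited pain cut (above 4 versus below 5) falls inside the eligible range, so the variable still varies among enrolled women.

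Prevention of CRPS is the trial's motivating question, and only about 60 women are expected to be evaluable. The test therefore asks for stronger evidence than the stated level and leaves information already collected unused.

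**Working it through.** **Inputs.** From the article: 20% versus 58%; two-sided 0.05; 30 evaluable and 33 enrolled per arm; ratio 15.1; entry above 3/10. Assumptions: n = 30 also applies to the CRPS power sentence; the share of women rated exactly 4 (10% to 50%); the pain–CRPS odds ratio within the enrolled range (1 to 15.1, reading the cited ratio as an odds ratio).

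**Step 1: reproduce the plan's figure.** Sum over all tables with a events of n in one arm and b of n in the other:

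Power = Σ Bin(a; n, 0.58) · Bin(b; n, 0.20) · 1[Fisher p(a,b) < 0.05].

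At n = 30 this is 80.97%, matching the stated 81%. That also supports 30 as the missing number. The pooled normal approximation would give Φ[(0.38·√30 − 1.96·√(2·0.39·0.61)) / √(0.20·0.80 + 0.58·0.42)] = Φ[(2.081 − 1.352)/0.635] = Φ(1.148) = 87.5%, so the stated 81% agrees with Fisher's test and not with this approximation.

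**Step 2: true size.** Use the same sum with a common rate π in both arms, maximised over π. At 30 per arm the maximum is 2.7% (2.6% at the mid rate of 39%). At 33 per arm it is 3.6% (3.1% at 39%).

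**Step 3: an exact test that uses more of the 5%.** Boschloo's test rejects when Fisher's p falls at or below a cut-off chosen so that the maximum size stays within 5%. The cut-off is 0.0692 at n = 30 and 0.0769 at n = 33.

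| Per arm | Fisher power | Boschloo power (max size) | Gain |
|---|---|---|---|
| 30 | 81.0% | 86.7% (4.7%) | 5.7 points |
| 33 | 86.6% | 90.1% (4.9%) | 3.5 points |

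**Step 4: adjust for pain.** Cochran-Mantel-Haenszel (CMH) test, two strata (4 versus 5 or more), no continuity correction: [Σ(observed − expected)]² / Σ variance > 3.841. It was simulated with the overall rates held at 20% and 58%, 30 per arm. Gains are against Fisher's exact 81.0%.

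| Pain odds ratio | Share rated 4 | CMH power | Gain |
|---|---|---|---|
| 1 (not prognostic) | any | about 87% | about 6 |
| 1.5 to 3 | 5% to 50% | 87.0% to 88.7% | 6 to 8 |
| 5 | 10% to 50% | 88.7% to 90.3% | 8 to 9 |
| 15.1 | 10% | 88.8% | 8 |
| 15.1 | 20% | 90.7% | 10 |
| 15.1 | 35% | 93.6% | 13 |
| 15.1 | 50% | 94.6% | 14 |

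Simulated size with both arms at 39% was 4.6% to 5.7% over 6,000 runs per setting (Monte Carlo standard error about √(0.05·0.95/6000) = 0.3 points), and 4.8% to 5.3% in a run of 20,000. With pain as a continuous covariate in logistic regression and odds ratios per SD of 1.5, 2, 3 and 4, Wald-test power was 87.8%, 89.4%, 92.6% and 94.1%.

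At 33 per arm, CMH power was 92.1% to 96.9% (odds ratio 5 or 15.1, share 20% or 50%), against 86.6% for Fisher: a gain of about 5 to 10 points.

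**The case against.** The strongest reply is that nothing here is an error. The trial was sized for the test it will use, Fisher controls type I error, and it is a conventional choice at this size. That stands. A reader might infer from the low true size that the 81% is overstated or the trial underpowered; Step 1 shows it is neither.

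Several other stronger readings also fail:

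- *Size below 3% as a general statement.* It holds at 30 per arm. If all 33 per arm are evaluated, which is the article's own retention goal, the maximum is 3.6% and the exact-test gain falls to 3.5 points.
- *Pain as the protocol's strongest known predictor.* The article quotes ratios of 5.8, 7.7 and 15.1 for different factors but never ranks them.
- *The full 15.1 applying inside the trial.* The cited comparison group includes ratings 0 to 3, which entry excludes. No figure is given for 4 versus 5 or more.
- *A gain of 14 points.* That needs the full 15.1 and about half the women rated exactly 4. The Background reports severe or very severe pain in 81% at first follow-up, which suggests that few may sit at 4, although those words are not mapped to the numerical scale.

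Conservatism also has some merit here: there are three primary outcomes, each tested at 0.05, and CRPS is assessed at three visits. A test running under 3% adds less to the overall false-positive risk. This is a real cost of the change.

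It could also be said that covariates belong in an unseen analysis plan. But the article does fix the primary CRPS test, and that test cannot take a covariate. Comparing baseline characteristics between arms would reveal an imbalance in pain but not correct it.

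**Conclusion.** The point holds as avoidable inefficiency in a valid, correctly powered analysis. At 30 evaluable per arm, Fisher's test has a maximum size of 2.7% and 81.0% power, and a pain-adjusted test would have about 87% to 91%, a gain of about 6 to 10 points. Roughly 6 of those points come from leaving Fisher and need no assumption about pain. The remainder rests on the strength of the pain–CRPS association among women rated 4 to 10 and on the share rated 4, neither of which the article gives. The simulations show no loss against Fisher even if pain proves uninformative. The change is worth making because it is cheap; the trial is not invalid without it.

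**What to change.** In the Statistical analysis section, before unblinding, replace the CRPS sentence along these lines: the primary comparison of CRPS diagnoses is adjusted for the baseline pain rating, by a CMH test stratified by rating 4 versus 5 or more, or by logistic regression on the rating (choose one and state it). Report the adjusted risk difference with a 95% CI. Keep Fisher's exact test as sensitivity analysis and as the named fallback, with a stated rule for when a stratum counts as too sparse.

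If the sponsor prefers no adjustment, Boschloo's test alone recovers 5.7 points at 30 per arm (3.5 at 33) with strict size control. Choosing it over Fisher is optional.

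Cost: a few sentences, with no new patients or measurements, provided the eligibility pain rating is kept in the analysis dataset. Downsides: the comparison then spends the full 5% instead of under 3%, the adjusted test is asymptotic, and the stratum of women rated 4 may be small.

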### Outcome measurements

All outcome measures will be administered by a single licensed OT who will be blinded to allocation. Blinded assessments occur within 1 week of cast immobilization (baseline), at four three weeks post cast immbolization, cast removal, and at three months post cast removal. A list of measures and a timeline of all data collection points can be found in Table 2.

**Table 2 Tab2:** Data collection time points

		Baseline (Immediately prior to Starting Therapy)	3 weeks post casting	Week of Cast Removal	4 weeks after cast removal	12 weeks after cast removal
Primary Outcomes	McGill Pain Scale	X	X	X	X	X
	Patient Rated Wrist Evaluation			X	X	X
	Assessment of CRPS I (Budapest criteria)			X	X	X
Secondary Outcomes	Finger Edema (%Unaffected)	X (Affected and Unaffected)	X	X	X	X
	Wrist/Forearm Goniometry (%Unaffected)	X (Unaffected)		X	X	X
	Grip Strength (%Unaffected)	X (Unaffected)			X	X
	Therapy Adherence Log		X	X		
	Patient’s Global Impression of Change			X		
	Continued Hand Therapy Sessions				X	X
	Pain Medication Use	X	X	X	X	X
	Blinding Questionare			X		

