#### Primary outcomes

##### PRWHE

The PRHWE [15] is a 15-item questionnaire designed to measure wrist pain and disability in activities of daily living. The PRHWE allows patients to rate their levels of wrist pain and disability from 0 to 10, and consists of 2 subscales: 1) Pain subscale: contains 5 items each of which is further rated from 1 to 10. The maximum score in this section is 50 and minimum 0; 2) Function subscale: contains total 10 items which are further divided into 2 sections i.e. specific activities (having 6 items) and usual activities (having 4 items). The maximum score in this section is 50 and minimum 0. The PRWHE is a widely-used instrument with sound psychometric properties and an established minimum clinical important difference (MCID) after DRF [15, 54, 55] of 11.5 points. The PRWHE has demonstrated higher responsiveness to change after DRF than the DASH questionnaire, as indicated by a higher standardized response mean (SRM) over three and six month periods [55].

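### The PGIC anchor is collected only at the visit where the PRWHE is first measured, so a valid anchor-based MCID for the PRWHE cannot be calculated as scheduled

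*Protocol article*

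**What the plan says.** The Statistical analysis section states that an "achor-based approach to determining the MCID of the PRWHE and SF-MPQ will be taken". The anchor is the PGIC, a seven-point rating that runs from very much improved to very much worse, "and will be administered at the time of cast removal". No other PGIC time is named.

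The Outcome measurements section makes Table 2 the schedule: "A list of measures and a timeline of all data collection points can be found in Table 2". Three of its rows matter here.

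- "Patient’s Global Impression of Change": one mark, in the week of cast removal.
- "Patient Rated Wrist Evaluation": marks at cast removal and at 4 and 12 weeks afterwards; the baseline and 3-week cells are empty.
- "McGill Pain Scale": marks at all five visits, baseline included.

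The PRWHE subsection under Primary outcomes says that the instrument already has "an established minimum clinical important difference (MCID) after DRF", and gives it as 11.5 points.

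**The concern.** An anchor-based MCID links a patient's global rating of change to the change in the instrument's score over the same period. Both the rating and the score change have to exist, and they have to cover the same interval.

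A PGIC answered at cast removal rates change up to that day. If the PRWHE is measured for the first time on that day, it has a level but no change to set against the rating.

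At stake is an analysis that the article announces for one of its primary outcome measures. If the trial runs to Table 2, the data needed are never collected, and no later choice of analysis method can supply them.

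**Working it through.** The plan states no MCID result to reproduce, so the check compares the schedule with what the method needs.

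**Inputs.** The visit marks come from Table 2, and the anchor and its timing from the Statistical analysis section.

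| Measure | Baseline | 3 weeks | Cast removal | 4 weeks after | 12 weeks after |
|---|---|---|---|---|---|
| PGIC | – | – | X | – | – |
| PRWHE | – | – | X | X | X |
| SF-MPQ | X | X | X | X | X |

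**Step 1: change scores that end at the PGIC visit.** A usable pair needs a score at cast removal and one at an earlier visit.

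- PRWHE: 0 earlier visits, so 0 pairs.
- SF-MPQ: 2 earlier visits, so 2 pairs (baseline to cast removal; 3 weeks to cast removal).

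**Step 2: PRWHE change scores that do exist.** There are three: cast removal to 4 weeks, cast removal to 12 weeks, and 4 to 12 weeks. All lie after the only PGIC. A rating given before a change has happened cannot anchor that change, and no PGIC is collected at 4 or 12 weeks.

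**Step 3: a cross-sectional substitute.** PRWHE levels at cast removal could be compared across PGIC categories. That describes how levels differ between patients who rate themselves differently. It does not give an MCID for change.

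**Step 4: number of contributors.** As scheduled, 0 of 66 participants can contribute to a PRWHE MCID. With a PGIC at 4 or 12 weeks, up to 66 could contribute for each interval. At the article's 10% dropout this is 66 × 0.90 = 59.4, in line with the 2 × 30 = 60 assumed in the sample size.

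**Step 5: is the main analysis touched?** The article gives 81% power for a 0.75 SD difference in change with 30 per group. A two-sample t-test at two-sided 0.05 gives 81.5%, so the figure reproduces. No MCID enters that calculation.

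**The case against.** The strongest reply is that Table 2 may simply lack a mark. The table is not complete: joint position sense is described as a secondary outcome and listed for the mixed models, yet it has no row. The text above the table mentions a baseline assessment, the sample-size paragraph speaks of change in the PRWHE, and the Background cites PRWHE disability in the first week after fracture. If a baseline PRWHE was intended, the PGIC at cast removal would have a matching change score.

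This reading is possible but unlikely. The sentence on baseline assessment names no instrument and leads to Table 2. The PRWHE row has the same pattern as the Budapest row. The McGill pain scale subsection notes that the PRWHE pain items are tied to activity and that a measure without that feature is needed for an immobilized limb, which fits deliberate omission during casting. If the mark was omitted in error, the table still has to be corrected.

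A second reply is that the MCID work is a side exercise, absent from the objective and the hypothesis. That is true and limits the weight of the point.

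A reader might also infer more than the article supports:

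- **That the SF-MPQ MCID covers the wrong interval.** The hypothesis places pain and disability at 1 month after cast removal, but the primary objective also names the time following cast removal as a comparison point. Baseline to cast removal is therefore a relevant interval.
- **That the minimal detectable change fails too.** The article takes that method from a cited study and does not say that it uses the PGIC.
- **That the group difference loses its benchmark.** Nothing says that it will be judged against an MCID estimated in the trial. The stated criterion is a two-sided p-value below 0.05, and 11.5 points is already cited.

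**Conclusion.** The point holds for the PRWHE MCID only. The article fixes the instrument, the anchor and the anchor's visit, and its own schedule leaves no PRWHE change score over the interval that the anchor rates. As scheduled, 0 of 66 participants can contribute, so no valid anchor-based PRWHE MCID can be calculated.

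This rests on two assumptions: that Table 2 shows the intended PRWHE visits, and that the PGIC asks about change up to the day it is given, as its response scale implies.

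The plan should be corrected, but the consequence is contained. The SF-MPQ MCID is feasible. The treatment comparison, the sample size and the power do not depend on this analysis. No conclusion is drawn about the minimal detectable change.

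**What to change.** Choose one of three and bring the Statistical analysis section and Table 2 into line.

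1. Add the PGIC at the existing 4-week and/or 12-week visits, worded with cast removal as its reference point, and anchor PRWHE change from cast removal to those visits. Keep the PGIC at cast removal for the SF-MPQ.
2. If a baseline PRWHE was intended, correct Table 2 to show it. The PGIC at cast removal then has a matching PRWHE change.
3. Drop the PRWHE from the MCID aim and rely on the 11.5 points already cited in the PRWHE subsection.

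The first option costs one extra question at one or two visits that already take place. Its drawback is that the resulting MCID describes recovery after cast removal, not change during the six-week intervention, and the text should say so. The third costs only an edit to the text. None of the three changes the sample size.

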**Methods/design:**

This article describes a six-week randomized comparative effectiveness trial, where the outcomes of a modified GMI program (mGMI) + standard of care (SOC) group (*n* = 33) are compared to a SOC only control group (*n* = 33). Immediately following cast immobilization, both groups participate in four 1-h clinic-based sessions, and a home program for 10 min three times daily until cast removal. Blinded assessments occur within 1 week of cast immobilization (baseline), at three weeks post cast immbolization, cast removal, and at three months post cast removal. The primary outcomes are patient reported wrist/hand function and symptomology on the Patient Rated Wristand Hand Evaluation, McGill Pain Questionnaire, and Budapest CRPS Criteria. The secondary outcomes are grip strength, active range of motion as per goniometry, circumferential edema measurements, and joint position sense.

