## Methods

### Objectives and hypotheses

#### Primary objective

To determine if women at risk for CRPS development after closed treatment of DRF who participate in a mGMI and SOC hand therapy have differing function, pain, upper limb impairments, and counts of CRPS diagnoses following cast removal, and at 1 and 3 months when compared to those who receive only the SOC.

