#### Hypothesis

We hypothesize that the combined GMI/SOC intervention will have a positive effect on disability, pain and upper limb impairments at 1 month following cast removal, and counts of CRPS diagnoses at 3 months post cast removal when compared to SOC alone.

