##### Budapest CRPS type I diagnostic criteria

A clinical assessment of CRPS presence will be conducted via use of the Budapest CRPS Type I Diagnostic Criteria [57]. These diagnostic criteria were selected over all others due to relatively higher inter-rater reliablity specificity [57]. Given that the timeframe for onset of CRPS after closed treatment of DRF has been found to be one to three months following cast removal [25], participants will be assessed upon cast removal, four weeks post removal and 12 weeks post removal. This assessment will be performed by a board certified orthopaedist with Hand Surgery training. These diagnostic criteria are presented in Table 3.

**Table 3 Tab3:** Budapest diagnostic criteria

The patient must: 1. Have continuing pain, which is disproportionate to any inciting event 2. Report at least one symptom in three of the four following categories: • Sensory: reports of hyperesthesia and/or allodynia • Vasomotor: reports of temperature asymmetry and/or skin color changes and/or skin color asymmetry • Sudomotor/edema: reports of edema and/or sweating changes and/or sweatingasymmetry • Motor/trophic: reports of decreased range of motion and/or motor dysfunction (weakness, tremor, dystonia) and/or trophic changes (hair, nail, skin) 3. Display at least one sign at time of evaluation in two or more of the following categories: • Sensory: evidence of hyperalgesia (to pinprick) and/or allodynia (to light touch and/or deep somatic pressure and/or joint movement) • Vasomotor: evidence of temperature asymmetry and/or skin color changes and/or asymmetry • Sudomotor/edema: evidence of edema and/or sweating changes and/or sweating asymmetry • Motor/trophic: evidence of decreased range of motion and/or motor dysfunction (weakness, tremor, dystonia) and/or trophic changes (hair, nail, skin) 4. Not have another diagnosis that better explains the signs and symptoms	

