### Adverse events

At each contact with the participant, the will seek information on adverse events by specific questioning and, as appropriate, by examination. Information on all adverse events will be recorded immediately in the source document, and also in the appropriate adverse event module of the case report form (CRF). All clearly related signs, symptoms, and abnormal diagnostic procedures results will be recorded in the source document. Reports of all serious adverse events (including follow-up information) will be submitted to the IRB within 10 working days if it falls under the UPIRTSO guidelines. Copies of each report and documentation of IRB notification and receipt will be kept in the Clinical Investigator’s binder. A second copy will be sent to the sponsor.

The PI will be responsible for 1) collecting, reporting, and risk management of adverse events, 2) data collection, entry, transmission and analysis, 3) site coordination and enrollment, 4) regulatory issues such as IRB actions, and conflict of interest disclosures, and 5) reporting the interim analysis to IRB. All collaborators will be immediately notified of any adverse events occur.

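### Three unranked primary outcomes are each judged at two-sided 0.05 with no rule for trial success, and the analysis names no decisive visit or contrast

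*Protocol article*

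**What the plan says.** - **Primary outcomes.** The Abstract (Methods/design) states: "The primary outcomes are patient reported wrist/hand function and symptomology on the Patient Rated Wristand Hand Evaluation, McGill Pain Questionnaire, and Budapest CRPS Criteria". Table 2 and the Primary outcomes subsection list the same three. None is ranked above the others.
- **Significance level.** The end of the Statistical analysis section states that two-sided tests with a p-value "less than 0.05 will be considered statistically significant". No order of testing, split of alpha or requirement that all three succeed is given.
- **Times in the objective.** Function, pain, impairments and "counts of CRPS diagnoses following cast removal, and at 1 and 3 months".
- **Times in the hypothesis.** Benefit is expected for disability and pain, together with "upper limb impairments at 1 month following cast removal, and counts of CRPS diagnoses at 3 months post cast removal".
- **Times in the analysis.** None. PRWHE and SF-MPQ each get a mixed model with group, time and group-by-time terms, and no term or visit is called decisive. CRPS gets Fisher's exact test, although "participants will be assessed upon cast removal, four weeks post removal and 12 weeks post removal".
- **Sample size.** 30 per group gives 81% power for a 0.75 SD difference in the continuous primaries. The article also gives 81% power for 20% vs 58% on CRPS; the group size is blank in that sentence. Enrolment is 33 per group to allow for 10% dropout.

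**The concern.** The article sets the threshold for each test but not what counts as success of the trial. With three co-equal primaries, a positive result on any one of them can be presented as meeting the primary objective, and the chance of at least one false positive is then above the nominal 5%.

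The open contrast adds to this. Objective and hypothesis give different times, and the analysis chooses neither. In the mixed model either the group term or the interaction could later be called the test. For PRWHE the choice matters: Table 2 shows no baseline PRWHE, so a difference already present at cast removal and constant afterwards would appear in the group term and not in the interaction. The SF-MPQ section also describes sensory and affective subscales, a present-pain item and a VAS, and names none of them as the primary score.

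Because the trial is sized at unadjusted 0.05, adding a correction later would lower the stated power.

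**Working it through.** **Inputs.** Three primaries, two-sided alpha 0.05, 30 evaluable per group, 0.75 SD, and 20% vs 58%, all from the article. Two assumptions are added: 30 per group for CRPS, because the number is blank, and the correlations between test statistics, because the article gives none.

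**1. Reproduce the stated power.**
- Two-sample t-test, n = 30 per group, d = 0.75, alpha 0.05: 81.5%.
- Exact power of Fisher's test, n = 30 per group, 20% vs 58%, alpha 0.05: 81.0%.

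Both match the stated 81%, so both rest on an unadjusted 0.05.

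**2. Family-wise error, one test per primary, any success counts.**
- Independent tests at full size: 1 − 0.95³ = 0.1426, or 14.3%.
- Fisher's test is conservative. Its true size at 30 per group is about 2.2–2.6% for null rates from 20% to 58%. At a null rate of 37% the size is 2.56%, and 1 − 0.95² × (1 − 0.0256) = 0.1206, or about 12%.
- Correlated tests (multivariate normal simulation, common correlation assumed):

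| Correlation | All three at 5% | CRPS at about 2.6% |
|---|---|---|
| 0.3 | 13.6% | 11.6% |
| 0.5 | 12.6% | 10.7% |
| 0.7 | 10.9% | 9.4% |
| 0.9 | 8.4% | 7.3% |

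The overall range is about 7–14%.

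**3. Power if alpha is divided by three.** Alpha = 0.05/3 = 0.0167.
- 0.75 SD, t-test, n = 30: 67.0%.
- 20% vs 58%, Fisher, n = 30: 66.2%.

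Restoring 81% at this level takes about 40 evaluable per group for the continuous outcomes and about 39 for CRPS. With 10% dropout, 40/0.9 = 44.4, so about 45 enrolled per group against the planned 33.

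**The case against.** The strongest reply is that a family-wise rule and a named contrast are things an article leaves to the full protocol or analysis plan, and that 0.05 is an ordinary per-test level which does not say one success is enough. Part of this stands: a rule may exist elsewhere, and if all three primaries had to succeed there would be no inflation. But the article itself states the threshold and sizes the trial on it. An unseen plan that split alpha would lower the stated 81%, and it could not remove the difference between the objective and the hypothesis.

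It is also fair that the hypothesis can be read as the confirmatory claim, with its times already fixed. That makes the repair easy, but the analysis section does not take those times up.

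Three stronger readings are tempting and are not supported:

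- **Ten looks.** Table 2 schedules PRWHE three times, SF-MPQ four times after baseline and CRPS three times. A reader might count 3 + 4 + 3 = 10 tests and infer an error of about 28–31% under assumed correlations. That is a measurement schedule, not a testing schedule. The mixed model is compatible with one test per continuous outcome, and neither the objective nor the hypothesis names the week-3 visit.
- **Interim analysis.** The Adverse events section gives the PI the duty of "reporting the interim analysis to IRB". A reader might infer an efficacy look that spends alpha. The mention stands among adverse-event and regulatory duties, and no efficacy look or stopping rule is stated.
- **Missing 4-week visit.** The prose of the Abstract and of Outcome measurements goes from "cast removal, and at three months post cast removal" without the 4-week visit. A reader might infer that the visit is in doubt. Tables 1 and 2 and the SF-MPQ and Budapest sections all include it, so this is an editorial slip with no bearing on false-positive risk.

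**Conclusion.** The point holds. Three unranked primaries are each judged at two-sided 0.05, the power figures depend on that level, and the decisive visit and contrast are left open between an objective and a hypothesis that differ. If any single success counts, the family-wise error is about 7–14% with one test per outcome. The upper end assumes independence and full test size. The lower end assumes a correlation of 0.9 and allows for Fisher's conservatism. Across that range it stays above 5%. Separate tests at each visit would raise it further, but the text does not commit to them, so no larger figure is claimed. The CRPS figures rest on an assumed 30 per group.

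**What to change.** Before unblinding:

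1. Name one confirmatory contrast per primary at the hypothesis's own time: PRWHE at 4 weeks, one named SF-MPQ score at 4 weeks, and CRPS at 12 weeks, all after cast removal. State which model estimate gives the contrast for the two continuous outcomes.
2. Test the three in a pre-stated order, each at two-sided 0.05, stopping at the first non-significant result. Alternatively use Holm, and state that power for a single outcome can be as low as about 66–67% at 30 per group (the 0.05/3 step).
3. Report all other visits and outcomes as estimates with confidence intervals.
4. Bring the objective, the hypothesis and the analysis section into line on these times.

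The change is to wording only, and the planned 66 participants can stay. The price of a fixed order is that a later outcome cannot be claimed if an earlier one fails. With the two continuous outcomes first and independent tests, the chance of reaching and passing the second is 0.815² = 66%, and the third 0.815² × 0.810 = 54%; positive correlation raises both. The documents do not settle the order, so the investigators should choose it and give the reason.
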